## Abstract

Background: Molar incisor hypomineralisation (MIH) is a common disorder of tooth development, which has recently been found to be associated with a higher prevalence of hypodontia. The aim of this international multicentre study is to determine the association between MIH and other developmental anomalies in different populations. Methods: Investigators were trained and calibrated for the assessment of MIH and dental anomalies and ethical approvals obtained in each participating country. The study aimed to recruit 584 children with MIH and 584 children without MIH. Patients aged 7–16 years who attend specialist clinics will be invited to participate. Children will undergo a clinical examination to determine the presence and severity of MIH, using an established index. The presence of any other anomalies, affecting tooth number, morphology, or position, will be documented. Panoramic radiographs will be assessed for dental anomalies and the presence of third permanent molars. Statistical analysis, using a chi squared test and regression analysis, will be performed to determine any differences in dental anomaly prevalence between the MIH and non-MIH group and to determine any association between dental anomalies and patient characteristics. Conclusion: This large-scale study has the potential to improve understanding about MIH with benefits for patient management.

## 1. Introduction

### 1.1. Background and Rationale

One of the most common disorders affecting tooth formation is molar incisor hypomineralisation (MIH), a variable developmental hypomineralised defect of enamel involving the first permanent molars and often the incisors, with an estimated global prevalence of 13% [1]. The management of children with MIH presents numerous challenges relating to the sensitivity and post-eruptive breakdown of affected molars, poor enamel bonding characteristics, and psychosocial concerns about incisor opacities [2,3]. Despite its common occurrence, speculation still surrounds its aetiology, as it is likely that several systemic and genetic and/or epigenetic factors are involved [4]. Within paediatric dental practice, a wide variety of other anomalies in tooth development are also seen, namely, relating to tooth number, morphology, and eruption. The reported prevalence of each of these different dental anomalies is highly variable, depending on the diagnostic criteria employed, as well as the characteristics of the study population [5,6]. Some dental anomalies, notably tooth number, appear to have a gender predilection; supernumerary teeth are twice more common in males than females, whereas hypodontia is more common in females than males [5]. Studies have also reported potential ethnic variation in the presentation of certain developmental dental conditions, with a systematic review reporting significant worldwide disparity in hypodontia prevalence, ranging from 4.4% in Latin America/Caribbean to 13.4% in Africa [7]. Most studies appear to show no gender difference in MIH but, to date, differences according to ethnicity have not been fully explored [1].

From a clinical perspective, it is important to recognise the potential for more than one oral/dental anomaly to be present in the same patient [8,9,10,11,12,13,14]. For example, children with a cleft lip and/or palate have a significantly higher incidence of hypodontia, not only in the region of the cleft, but in the whole dentition [15]. Another example of anomaly co-occurrence relates to hypodontia and taurodontism; children with congenitally missing teeth appear to have a significantly higher prevalence of taurodontism (34.8%) than their unaffected peers (7.5%) [16]. The potential for other anomalies to occur in children with MIH has only recently been recognised. An observational study of 101 children with MIH, conducted in a UK dental hospital, showed that 29% of patients had an additional dental anomaly [17]. The key finding was of a high prevalence of hypodontia, which affected 12% of the MIH patients (16.1% of girls and 2.6% of boys). These findings sparked interest amongst the international paediatric dentistry community.

In view of the important clinical and biological implications of any co-existence between MIH and other disorders of dental development, it was proposed that a multicentre international study (iMIH) should be undertaken to explore this preliminary finding further. The collaborative study would have additional value in determining any country/ethnic-related variations in the presentation of MIH and other dental anomalies, using a standard diagnostic approach. This paper describes the protocol for the planned study, including details of investigator training and calibration. The protocol was prepared according to guidance provided in the SPIRIT 2013 Checklist [18].

### 1.2. Aim and Objectives

The overall aim of this international multicentric analytical cross-sectional study is to explore any association between MIH and other developmental dental anomalies.

The primary objective is to:compare the overall prevalence of a dental anomaly (specifically hypodontia) in the permanent dentition of children (seven to sixteen years-of-age) with and without MIH.

The secondary objectives are to: determine the prevalence of other developmental dental anomalies, including: microdont maxillary lateral incisors; dens invaginatus/evaginatus; double teeth; supernumerary teeth; infraocclusion of primary molars; hypomineralisation of second primary molars; ectopic (palatal) position of maxillary canines; ectopic/failed eruption of first permanent molars, and taurodontism of mandibular first permanent molars and investigate the influence of gender and ethnicity/country;measure children’s self-reported global evaluation of their oral health in relation to their dental condition.

### 1.3. Null Hypothesis

There will be no significant difference in the prevalence of dental anomalies in children with or without a diagnosis of MIH.

## 2. Materials and Methods

### 2.1. Overall Study Design

This will be a cross-sectional analytical study involving children with MIH and a comparison group of non-MIH-affected children.

### 2.2. Establishment of the Investigatory Team and Study Setting

Following the publication by Walshaw and colleagues (2020) [17], which first suggested an increase in hypodontia prevalence in children with MIH, several paediatric dentists with an interest in MIH formed a collaborative research group to explore this association further. [name] (UK) and [name] (Qatar) took on the role of joint primary investigators for the study, and a core group (named co-authors on this paper) was established to develop the protocol through a series of online meetings (held during 2020/21). The final investigatory team involved 22 senior paediatric dentistry colleagues across 15 countries (Australia; Chile; Egypt; Jordan; India; Netherlands; New Zealand; Nigeria; Qatar; Saudi Arabia; Singapore; Sudan; United Arab Emirates; United Kingdom; United States of America). The study will take place at specialist paediatric dentistry clinics in both teaching hospitals and community settings.

### 2.3. Eligibility Criteria

Participants are children, aged seven to sixteen years-old, with and without MIH, who meet the inclusion criteria, and who are attendant for assessment or treatment in the participating clinics. To avoid bias, the comparison group will not be solely drawn from a pool of orthodontic patients or those primarily referred with a known diagnosis of dental anomalies.

Generic inclusion criteria—all participants (both MIH and comparison groups):No significant medical history (ASA ≤ 2), syndromic conditions, cleft lip and/or palateHave an existing (full) panoramic radiograph at recruitment or subsequently undergoes one for routine diagnostic purposesChild able to accept detailed clinical examination, radiographs, and photographsParents and children are able to consent/assent to participate in the study and have a sufficient level of literacy/understanding to complete written consent forms (with support if necessary).

MIH-group specific inclusion criteria:Children diagnosed with MIH by a specialist in paediatric dentistry according to validated diagnostic criteria [19,20]

Comparison-group specific inclusion criteria: Children referred to the host centre for the management of any dental condition other than MIHMIH-group specific exclusion criteria:Children with an enamel defect that is not typical of MIHComparison-group specific exclusion criteriaChildren with an atypical pattern of dental caries/extraction in their first permanent molars such that a possible diagnosis of MIH could not be excluded [19,20]

### 2.4. Interventions

This study does not involve any intervention, as such. Participants will receive routine care, as deemed appropriate by the responsible clinician.

### 2.5. Outcomes

The primary outcome measure for this study is the presence or absence of MIH and its association with the presence of another dental anomaly (specifically hypodontia) in the participants. Details of the index used to score the enamel defect are described in Section 2.8 below.Secondary outcome measures for this study include the clinical and/or radiographic severity of MIH in relation to participants’ gender, ethnicity/country, and their global self-reported oral health, details of which are also provided in the subsequent Section 2.8.

### 2.6. Timeline and Participant Involvement

Recruitment of participants has commenced on a rolling basis in individual countries, according to the date on which ethical approval was obtained for that site. No change to the protocol was advised by any of the ethical committees. The first participant was recruited on 6 March 2022, and recruitment is scheduled to continue until 31 July 2023. The burden on the participants is minimal because, according to informed consent, participants simply undergo a clinical and radiographic examination as part of their normal scheduled appointment. No additional visits are required, and participants are only asked to answer two questions about their oral health status. It is expected that the study will be completed by December 2023.

### 2.7. Sample Size

Based on the prevalence estimates of hypodontia in MIH (0.12 [17]) and non-MIH children (0.064 [7]), a sample size of 1168 children (584 per group) would provide 90% power in detecting the statistically significant difference in the association between MIH and hypodontia. The alpha error was set at 5%. Each of the 15 participating countries would, therefore, aim to recruit approximately 80 children (40 MIH and 40 non-MIH). This sample size was calculated using the G Power software (Version 3.1.9.7).

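### The 12% hypodontia rate behind the stated 90% power does not reconcile with the sex-specific rates that the protocol gives for the same 101 children

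*Protocol article*

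**What the plan says.** Section 2.7 (Sample Size) takes the planning rates from two cited sources: "Based on the prevalence estimates of hypodontia in MIH (0.12 [17]) and non-MIH children (0.064 [7"]). It concludes that "a sample size of 1168 children (584 per group) would provide 90% power", with alpha at 5%, and names G Power as the software. Each of the 15 countries is then to "aim to recruit approximately 80 children (40 MIH and 40 non-MIH"), which comes to 600 per group.

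Section 1.1 (Background and Rationale) describes the source of the 0.12, reference 17, as follows: "An observational study of 101 children with MIH". It says that hypodontia "affected 12% of the MIH patients (16.1% of girls and 2.6% of boys"). It gives neither the numbers of girls and boys nor the numbers of cases.

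**The concern.** An overall rate is the average of the girls' and boys' rates, weighted by their numbers. With 101 children and sex rates given to one decimal place, few whole-number counts are possible, so the overall rate can be checked. It does not come to 12%.

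This matters because the 12% is more than background. It is the MIH-group input for the sample size of the primary comparison. The difference to be detected is only 5.6 percentage points, so an error of one point in that input moves the power a good deal. If the primary result is not significant, readers will use the stated 90% power to judge how informative it is. Section 4 makes such a result plausible, since it says that early findings from some centres do not support the association.

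**Working it through.** **Inputs.** From Section 2.7: p1 = 0.12 (MIH), p2 = 0.064 (non-MIH), n = 584 per group, alpha = 0.05. Section 2.7 does not say whether the test is one- or two-sided. Two-sided is assumed here because it reproduces the stated n. From Section 1.1: 101 children, 12% overall, 16.1% of girls, 2.6% of boys. From Section 2.12: chi-square or Fisher exact test.

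**Step 1: reproduce the plan's figure.** Exact power of the two-sided Fisher test for 0.12 vs 0.064 is 0.89999 at 583 per group and 0.9005 at 584. So 584 is where the power reaches 90%, and the stated size fits this test.

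For the chi-square test (pooled z), with d = p1 − p2 and p̄ = (p1 + p2)/2:

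power = Φ{ [d − 1.96·√(2p̄(1−p̄)/n)] / √([p1(1−p1) + p2(1−p2)]/n) }

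With d = 0.056 and p̄ = 0.092: (0.056 − 1.96 × 0.01691) / 0.01683 = 1.357, so power = 91.3%.

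**Step 2: which counts fit the sex rates?** Among denominators up to 100:
- 16.1% arises only as 5/31, 9/56, 10/62, 14/87 or 15/93.
- 2.6% arises only as 1/38, 1/39, 2/76, 2/77 or 2/78.

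The pairs with a total of at most 101 are:

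| Girls | Boys | Total | Overall |
|---|---|---|---|
| 5/31 | 1/38 | 6/69 | 8.7% |
| 5/31 | 1/39 | 6/70 | 8.6% |
| 9/56 | 1/38 | 10/94 | 10.6% |
| 9/56 | 1/39 | 10/95 | 10.5% |
| 10/62 | 1/38 | 11/100 | 11.0% |
| 10/62 | 1/39 | 11/101 | 10.9% |

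Only the last row adds to 101. No row gives 12%, so dropping children with missing data does not help.

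**Step 3: could rounding explain it?** Solving 0.161g + 0.026(1 − g) = 0.12 for the share of girls g gives g = 0.094/0.135 = 69.6%, about 70 of 101. The list in step 2 has no girls' denominator near 70. Even 11.5%, the lowest rate that rounds to 12%, needs g = 0.089/0.135 = 65.9%, about 67 girls, and again none fits. 11/101 rounds to 11%.

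**Step 4: power at 584 per group against 0.064.**

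For 11/101: d = 0.04491, p̄ = 0.08646, and (0.04491 − 1.96 × 0.01645) / 0.01639 = 0.773, so chi-square power = 78.0%.

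| MIH rate | Fisher exact | Chi-square |
|---|---|---|
| 0.12 (as planned) | 90.1% | 91.3% |
| 12/101 = 11.9% | 88.9% | 90.3% |
| 11/100 = 11.0% | 77.2% | 79.7% |
| 11/101 = 10.9% | 75.4% | 78.0% |

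At the 600 per group implied by 15 × 40, 11/101 gives 76.6% (Fisher) or 79.1% (chi-square). For 90% power at 11/101, about 821 per group would be needed (chi-square), or 865 with continuity correction.

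**The case against.** The strongest reply is that Section 2.7 contains no error of its own. It uses 0.12, Section 1.1 reports 12% for the same reference, and the calculation is correct for that input. The clash lies wholly within one background sentence, and the sex-specific rates were never inputs to the sample size. All of this is true.

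Nor do the documents say which figure is wrong. With 62 girls and 39 boys, one more case gives 12/101 = 11.9%, which rounds to 12%. The misprint would then be a sex rate: 2/39 = 5.1% of boys or 11/62 = 17.7% of girls. A case of unrecorded sex could also close the gap (10/62 girls, 1/38 boys and one unclassified case make 12/101), but the article mentions no such child. A reader might infer from the sex rates that the trial simply has 75–78% power. The documents do not support that as an unconditional statement: it is one branch, and the other leaves the power essentially as claimed.

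It can also be said that a planning rate is only an assumption, that the gap is one case in 101, and that Section 2.12 plans an odds ratio with a 95% confidence interval, which will show the precision whatever power was planned. This limits the harm but does not remove it. The 0.12 is presented as an estimate from a named source, and the protocol's own account of that source does not bear it out.

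**Conclusion.** The point holds in a conditional form. As printed, 101 children, 12% overall, 16.1% of girls and 2.6% of boys do not reconcile, and the sample size rests on one of these figures. That the denominators 62 and 39 add to exactly 101 makes 11/101 the likelier count, but the article alone cannot settle it.

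The size depends on the answer. If 11/101 is right, the type II error at the planning values rises from about 10% to about 22–25%. If 12/101 is right, the loss of power is about one percentage point. This assumes a two-sided 5% test, 584 per group, the 6.4% comparison rate as stated, sex recorded for every child counted, and conventional rounding. The validity of the planned analysis is not affected.

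**What to change.** Check the numbers of girls, boys and hypodontia cases in the source study and correct Section 1.1 so that its overall and sex-specific rates agree. Then:

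- **If 11/101 is right**, restate Section 2.7, for example: *584 per group gives about 75% power (Fisher exact; 78% chi-square) for 10.9% vs 6.4%; 90% power applies to 12% vs 6.4%.* Keep the sample size.
- **If 12/101 is right**, correct the sex-specific rates in Section 1.1, or explain any child of unrecorded sex. Section 2.7 can stand, since power is 88.9% (Fisher) or 90.3% (chi-square).

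The cost is one look at the source and an edit of one or two sentences. No extra children are needed. In the first case the stated power becomes less favourable.

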### 2.8. Data Collection

A clinical record form (CRF) form was developed and piloted prior to commencement of the main study (Supplementary document S1). The following non-identifiable patient and clinical variables will be recorded for each participant:

#### 2.8.1. Participants’ Demographics

Age; gender; ethnicity/country as appropriate (White; Mixed/Multiple ethnic groups; Asian; Black; Arabic; and other minority ethnic groups [to specify]).

#### 2.8.2. Clinical Variables

-The primary dental diagnosis will be recorded for both MIH and comparison participants (e.g., the comparison group could include patients presenting with orthodontic concerns, dental caries, traumatic dental injury, oral pathology/oral medicine-related issues, tooth surface loss, periodontal condition, or no dental condition but medical/behavioural reason for referral).-Any known close family history (siblings or parents) of enamel defects, or missing or extra teeth, will be documented.-Any enamel defect will be recorded using the validated MIH index [19,20]. All permanent teeth and second primary molars will be included, with scores given according to the nature of the defect (MIH or non-MIH) and, for MIH teeth, the severity and extent of the defect will also be recorded.-Any other anomalies detected clinically will be noted, including: microdontia of permanent maxillary lateral incisors, dens invaginatus/evaginatus, double teeth, erupted supernumerary teeth, infraocclusion of primary molars (categorised as >1 mm below occlusal level of adjacent tooth/teeth), and ectopic eruption of first permanent molars.

#### 2.8.3. Participants’ Perspectives

To ensure children’s views are also sought, participants will be invited to answer two global oral health-related quality of life (OHRQoL) questions, using a 5-point Likert response, from the widely used and validated Child Perceptions Questionnaire [21]. These questions (Box 1) will be included in the CRF for each participant and the investigator will invite the child to respond.

Box 1Global oral-related quality of life questions to be completed by the participants [21].Would you say the health of your teeth, lips, jaws and mouth is:
  □Excellent  □Very good  □Good  □Fair  □PoorHow much does the condition of your teeth, lips, jaws
or mouth affect your life overall?
  □Not at all  □Very little  □Some  □A lot  □Very much

#### 2.8.4. Radiographic Characteristics

All participants must have a full panoramic radiograph of good diagnostic quality, as indicated for their routine care, and not taken solely for the purpose of this study. This can be obtained from the participant’s past dental records rather than needing to be taken at the time of recruitment as long as the radiograph was obtained when the patient was seven to sixteen years-of-age. The following variables will be recorded from the radiographic presentation.

-Presence of any developing third molars.-Hypodontia of permanent dentition (excluding third molars).-Presence of any supernumerary teeth (specifying number and location).-Presence of ectopic maxillary canines—this can only be coded ‘yes’ if patient has also had an additional intra-oral radiographic view.-Presence of ectopic first permanent molars (a positive result would include evidence of distal resorption of second primary molars even if the first permanent molars have erupted subsequently).-Any other anomaly that was not detected clinically (e.g., double tooth, dens invaginatus).-Any other findings of note (e.g., any anomalies seen in the primary dentition).

#### 2.8.5. Assessment of Taurodontism

For patients with mature apical development of their first permanent mandibular molars (10 years and older), an objective assessment of taurodontism will be carried out using digital measurements from panoramic radiographs. The technique and criteria, described by Seow and Lai (1989) [16], will be adopted. The ratio (taken from vertical measurements) of the crown and body: root will be determined. The following classification system will be used to determine the degree of any taurodontism:-Crown/body:root ratio < 1.1 = normal-Crown/body:root ratio 1.1–1.29 = hypotaurodontism-Crown/body:root ratio 1.29–2.00 = mesotaurontism-Crown/body:root ratio > 2.00 = hypertaurodontism

### 2.9. Clinical Photographs

Wherever possible, clinical images of the participants’ dentition (maxillary and mandibular occlusal views, anterior view, and lateral views) will be taken and securely stored electronically as part of the data archive, as well as to support future investigations.

### 2.10. Investigator Training and Calibration

Prior to the start of the study, training and calibration on the use of a validated MIH index, which is supported by the European Academy of Paediatric Dentistry, was delivered to the two PIs by one of the original developers of this index ([name], Clinical Senior Fellow, University of Melbourne, Australia) [19,20]. Following that, an online training programme was produced by the PIs using the same 20 clinical cases from the original training manual [20]. All investigators were required to complete this training before commencing recruitment.

Training and calibration for the collection of other clinical and radiographic parameters was delivered by [name] (Unit of Oral Health, University of Sheffield, UK). This training involved two pre-recorded presentations: one describing the various dental anomalies under investigation and the second describing the methodology for measuring taurodontism.

Inter-examiner and intra-examiner agreement was assessed following this training; investigators repeated the scoring for the various paraments two weeks after the initial exercise. All clinicians involved in recording these parameters were required to reach acceptable levels of repeatability (Cohen Kappa coefficient between 0.61 and 1.00).

### 2.11. Data Management

Data will be stored at each participating centre, in accordance with local policies and regulations. In general, collated data will be anonymised, encrypted, and stored on password-protected computers. Each unit will be responsible for anonymised electronic data entry for their participants (using Microsoft Excel spreadsheet software) and will send the complete data set securely to [name] and [name] for data analysis. Only the PIs will have access to the final study dataset.

